#### *Complications*

##### Complication graded according to Clavien-Dindo

Postoperative complications will be graded according to the Clavien-Dindo grading [6]: information regarding complications is collected after surgery during hospital stay, 10 days

postoperatively ( $\pm 2$  day) when the patients had their sutures removed by the trial personnel and 30 days ( $\pm 3$  days) postoperatively through review of the patients' medical records and by the planned telephone interview. The definitions can be seen in Table 4.

#### Deep surgical site infections

Deep surgical site infection postoperatively: Information regarding surgical site infections was collected 10 days postoperatively ( $\pm 2$  day) when the patients had their sutures removed by the trial personnel and 30 days ( $\pm 3$  days) postoperatively through review of the patient's medical records and at the planned telephone call to the patients. It was defined as deep incisional surgical site infection according to Centre for Disease Control and Prevention (CDC) [7], which can be seen in Table 5.

#### Intraabdominal abscesses

Intraabdominal abscess: Information regarding intraabdominal abscesses was collected 10 days postoperatively ( $\pm 2$  day) when the patients had their sutures removed by the trial personnel and 30 days ( $\pm 3$  days) postoperatively through review of the patient's medical records and at the planned telephone interview. It was defined as an organ/space surgical site infection according to CDC [7] and can be seen in Supplements, Table 5. If a collection was found but not drained, it is not regarded as an abscess by definition in the current trial.

#### Readmissions

Readmissions: Information was collected 30 days ( $\pm 3$  days) postoperatively by review of the patient's medical records and at the planned telephone interview. Only readmissions related to the surgery was registered; e.g. admission and treatment of a non-related condition was not be registered.

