## Outcomes

### Primary outcome

Total length of in hospital stay (measured in hours) was defined as from end of the surgery until discharge from the hospital plus length of stay during a possible readmission within 30 days from surgery. The latter was calculated based on a review of the patient's record 30 days postoperatively ( $\pm 3$  days).

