#### **Sample size**

The power calculation for the trial was as follows. The cumulative 30-day length of stay was expected to be 72 hours with a standard deviation of 12 hours in the control group. When  $\alpha$  was set at 0.05,  $\beta$  was set at 0.80, and an acceptable difference between the groups was set at 48 hours, a randomised design requires 4 patients in each group, a total of 8 patients. However, as we expected data not to be normally distributed and planned to use a quasi-randomised design [8,9], we decided to include 6 patients in each group, a total of 12 patients to ensure sufficient power.

A participant has concluded the trial when the 30-day postoperative follow-up has been conducted. Inclusion of participants in the trial will continue until a minimum of six participants in each study group have reached the 30-day follow-up with data for the primary outcome parameter, total length of stay. Thus, we planned to include six patients in each study group and only if the primary outcome was not available at 30-day follow-up, further patients were included to ensure data on the primary outcome on six patients in each group.

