## Endpoints

### Primary endpoint

The difference in total length of stay measured in hours will be compared between the intervention and the control group. Total length of stay was defined as from end of the operation until discharge from the hospital plus length of stay during a possible readmission

within 30 days from surgery. All randomised participants will be included in the analysis (intention-to-treat) if all data have been collected for 30 days postoperatively). The length of stay will be presented as a continuous numerical variable in the Result section of the manuscript. We expect that the data are not normally distributed due to the low number of participants, thus, medians and range for the intervention and control group will be presented. Furthermore, a Mann-Whitney U-test will be performed to compare the length of stay between the two groups.

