### **Missing data**

Missing data regarding the primary outcome, length of stay, will be excluded from the analysis as total length of stay was defined from the end of surgery until 30 days postoperatively.

Missing data in the secondary outcomes regarding the questionnaires (GIQLI and harms) will be treated as follows. All received GIQLI questionnaires regardless of the amount of missing data will be included. If the questionnaire was never received data will be excluded. All received questionnaires regarding harms will be reported regardless of missing data.

Missing data of the secondary outcomes complication and adverse events due to lack of 30th day contact with participant cannot be reported. If no dates have been registered for the secondary outcomes of convalescence the data are excluded from the calculations of the continuous numerical variables.

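### The primary outcome runs to day 30, but its readmission hours may be read from the record as early as day 27, and the SAP does not settle whether readmissions unrelated to surgery count

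*SAP*

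**What the plan says.** The SAP section Primary outcome measures total length of stay in hours from end of surgery to discharge, "plus length of stay during a possible readmission within 30 days from surgery". On the readmission part it says "The latter was calculated based on a review of the patient's record 30 days postoperatively", with a tolerance of three days in either direction. The section Primary endpoint repeats the definition, again without a limit by cause, and analyses participants "if all data have been collected for 30 days postoperatively". The section Missing data gives the end of the window: "total length of stay was defined from the end of surgery until 30 days postoperatively".

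The section Readmissions, under Secondary outcomes, uses the record review and the telephone interview at the same time point with the same tolerance, and states: "Only readmissions related to the surgery was registered; e.g. admission and treatment of a non-related condition was not be registered".

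The section Design describes a non-blinded trial in which each group was included at a different hospital. The section Sample size plans 6 patients per group, with a control stay "expected to be 72 hours with a standard deviation of 12 hours in the control group" and an acceptable difference of 48 h.

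**The concern.** Two things that fix the primary total are left loose.

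- **Observation window.** The outcome covers 30 days, but a review on day 27, 28 or 29 is within the plan and cannot see the remaining time. No section asks for a second look after an early review.
- **Which readmissions count.** The primary definition is silent on cause, while the only section that describes how readmissions are registered leaves out unrelated ones. Two analysts who both follow the SAP could give the same patient different totals. The SAP gives no criterion for relatedness. In an open trial with one hospital per arm, that leaves room for an unblinded judgement to decide which hours enter the primary comparison.

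With 6 patients per group, a single total can decide on which side of the significance threshold the result falls.

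**Working it through.** **The plan's own figure.** The SAP gives no figure for this point. The nearest is the sample size, used here only for scale. Inputs: difference 48 h, SD 12 h, α 0.05 (taken as two-sided; the SAP does not say) and power 0.80 (labelled β in the SAP). The t-test noncentrality is 48 / (12 × √(2/n)), which gives:

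- n = 2 per group: power 0.565
- n = 3: power 0.948
- n = 4: power 0.996

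Three per group would be enough. The stated 4 is close (8 against 6 in total), and nothing below depends on it.

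**Hours that a compliant review can miss.** For a review d days after surgery, unseen hours = 24 × (30 − d) when d is below 30, and none otherwise.

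- d = 27: 24 × 3 = 72 h
- d = 28: 24 × 2 = 48 h
- d = 29: 24 × 1 = 24 h
- d = 30 or later: 0 h

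Against the Sample size inputs, 72 h is 72/72 = 1.0 times the expected control stay, 72/48 = 1.5 times the acceptable difference and 72/12 = 6 standard deviations.

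**Which readmissions count.** Two readings are open:

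- Primary outcome and Primary endpoint stand on their own, and all readmission hours within 30 days count.
- The Readmissions section defines the term for the whole SAP, and only surgery-related hours count.

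The totals differ only for a patient who has an unrelated readmission. No sentence chooses between the readings.

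**What one patient can do to the primary test.** Let U be the number of the 6 × 6 = 36 pairs in which the intervention patient has the longer stay. Under the null hypothesis there are C(12,6) = 924 equally likely rank arrangements, and the exact two-sided p is 2 × (arrangements with a U this low or lower) / 924.

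- U = 0: 2 × 1/924 = 0.0022
- U = 5: 2 × 19/924 = 0.0411
- U = 6: 2 × 30/924 = 0.0649

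Illustration with assumed data: controls at 66, 68, 70, 74, 76 and 78 h; five intervention patients at 20, 22, 24, 26 and 28 h; a sixth with an index stay of 28 h and a 72 h readmission.

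- Readmission counted: 28 + 72 = 100 h, longer than all six controls, so U = 6 and p = 0.065.
- Readmission missed or left out: about 28 h, shorter than all six controls, so U = 0 and p = 0.002.

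The SAP calls p ≤ 0.05 significant, so the conclusion changes. The rank arithmetic is the same whether the hours are lost through an early review or through a decision on relatedness.

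**The case against.** The case against has several good parts.

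- **The Readmissions section governs a secondary outcome.** The primary outcome has its own record review. One may also read the Readmissions section as simply defining the term, so that only a cross-reference is missing. This stands to the extent that a reader who infers that unrelated hours were left out of the primary total goes further than the text. Nor does the SAP say that every readmission counts; it speaks of a possible one. The cause question is an unreconciled definition, not a demonstrated omission.
- **A late review.** A reader might infer that a review on day 33 adds hours after day 30, or that follow-up differs by up to 6 days between patients. The Missing data section ends the outcome at 30 days, so a late look should add nothing. The loss is one-sided and at most 3 days.
- **Completeness condition.** Primary endpoint requires complete 30-day data, and Sample size requires six patients per group to have reached the 30-day follow-up. Read literally, a patient reviewed only on day 27 would not qualify. This helps, but it does not clearly close the gap, because the SAP treats the contact between day 27 and day 33 as the 30-day follow-up.
- **Who judges relatedness.** A reader might infer that unblinded staff at each arm's own hospital decided this. The SAP does not say who judged it or where. Only the opportunity is established.
- **The p-values come from a constructed case.** They need fully separated groups otherwise and one patient who moves past all six comparators. They show that one readmission can change the result, not that it will.
- **A tolerance of three days on a 30-day contact is ordinary.** That is true for a telephone call. A record can be read later at no loss, so the tolerance serves no purpose there.

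**Conclusion.** The point holds in a bounded form. Under the SAP as written, a compliant record review can leave up to 72 h of the 30-day primary window unseen, and the SAP does not settle whether hours of unrelated readmissions belong to the primary outcome. The 72 h is an upper bound: it needs a review on day 27 and a readmission that fills the last three days. The SAP gives no rate of early reviews, of late readmissions or of unrelated readmissions, so the chance that the result is affected cannot be calculated. The effect on the test assumes the exact two-sided Mann-Whitney distribution with 6 against 6 patients and the assumed stays above. The sample size is not affected. Because the repair is almost free and protects the primary outcome, it should be made.

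**What to change.** 1. In Primary outcome, state that patient records are read on or after day 30, and that readmission hours count up to 30 × 24 = 720 h after end of surgery and not beyond. Keep the three-day tolerance for the telephone call only.
2. Reconcile Primary outcome and Primary endpoint with Readmissions by stating which readmissions count. All causes is preferable, because it needs no unblinded judgement of relatedness. Surgery-related readmissions can then be reported as a descriptive sensitivity result without a further test. If the sponsor prefers surgery-related readmissions for the primary outcome, both primary sections should say so and give the criterion for relatedness and who applies it.

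The cost is a few sentences in the SAP and re-reading up to 12 records. The downside of counting all causes is some noise from an unrelated readmission, which the descriptive sensitivity result would make visible.

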#### Reoperations

Reoperations: Information will be collected 30 days ( $\pm 3$  days) postoperatively by review of the patient's medical records and at the planned telephone interview.

### ***Convalescence***

#### Time to return to normal activities

Time to return to normal activities: This time point was determined either 10 days ( $\pm 2$  days) postoperatively when the patients had their sutures removed by the trial personnel or 30

days ( $\pm 3$  days) postoperatively through the planned telephone interview of the participants. The date was defined at the time point at which the participant could return to normal daily activities.

#### Period of sick leave

Period of sick leave (absence from work): This time point was determined either 10 days ( $\pm 2$  days) postoperatively when the patients had their sutures removed by the trial personnel or 30 days ( $\pm 3$  days) postoperatively through the planned telephone interview of the participants. The parameter was defined as the number of days from the operation to the time point at where the participant returned to work or school.

#### ***Adverse events***

Adverse events: registered by trial personnel during admission, 10 days ( $\pm 2$  days) postoperatively when the patients had their sutures removed by the trial personnel and 30 days ( $\pm 3$  days) postoperatively through review of the patient's medical records and at the planned telephone call to the patients.

#### **Sample size**

The power calculation for the trial was as follows. The cumulative 30-day length of stay was expected to be 72 hours with a standard deviation of 12 hours in the control group. When  $\alpha$  was set at 0.05,  $\beta$  was set at 0.80, and an acceptable difference between the groups was set at 48 hours, a randomised design requires 4 patients in each group, a total of 8 patients. However, as we expected data not to be normally distributed and planned to use a quasi-randomised design [8,9], we decided to include 6 patients in each group, a total of 12 patients to ensure sufficient power.

A participant has concluded the trial when the 30-day postoperative follow-up has been conducted. Inclusion of participants in the trial will continue until a minimum of six participants in each study group have reached the 30-day follow-up with data for the primary outcome parameter, total length of stay. Thus, we planned to include six patients in each study group and only if the primary outcome was not available at 30-day follow-up, further patients were included to ensure data on the primary outcome on six patients in each group.

## Baseline characteristics

The baseline characteristics will be presented as depicted in Table 1. Age, height, weight, body mass index, number of times preoperative antimicrobial agents were administrated, and length of surgery will be presented as continuous numerical variables. Sex will be presented as a dichotomous variable, where the number of females and proportion in % are presented. American Society of Anesthesiologists (ASA) score will be presented as ordinal variable, where the number and proportion in % of each category (I, II, III, IV) is given. We expect that the data is not normally distributed due to the few number of participants. Because of the quasi-randomised design, a difference between groups could arise, therefore, the p-value of statistical tests will be reported. The rationale of presented variables and the statistical tests used is presented in Statistical methods.

| Admission                                 | Intervention group (n=x) | Control group (n=x) | p-value                                     |
|-------------------------------------------|--------------------------|---------------------|---------------------------------------------|
| Age, years                                | x (x-x)                  | x (x-x)             | [from Mann-Whitney U-test]                  |
| Sex, female                               | n (%)                    | n (%)               | [from Chi-square-test/Fisher's exact test]  |
| Height, cm                                | x (x-x)                  | x (x-x)             | [from Mann-Whitney U-test]                  |
| Weight, kg                                | x (x-x)                  | x (x-x)             | [from Mann-Whitney U-test]                  |
| Body Mass Index, kg/m         | x (x-x)                  | x (x-x)             | [from Mann-Whitney U-test]                  |
| ASA score                                 |                          |                     | [from Chi-square-test /Fisher's exact test] |
| I:                                        | n (%)                    | n (%)               |                                             |
| II                                        | n (%)                    | n (%)               |                                             |
| II:                                       | n (%)                    | n (%)               |                                             |
| IV:                                       | n (%)                    | n (%)               |                                             |
| Preoperative antimicrobial agents* |                          |                     |                                             |
| Times administrated                       | x (x-x)                  | x (x-x)             | [from Mann-Whitney U-test]                  |
| Surgery                            |                          |                     |                                             |
| Length, hours:minutes                     | xx:xx (xx:xx-xx:xx)      | xx:xx (xx:xx-xx:xx) | [from Mann-Whitney U-test]                  |

*Table 1. Demographics of the xx included patients for continues variables in median (range) and for categorical variables in number (percent). ASA: American Society of Anesthesiologists [10]. \* Included the following antimicrobial agents: .*

## Endpoints

### Primary endpoint

The difference in total length of stay measured in hours will be compared between the intervention and the control group. Total length of stay was defined as from end of the operation until discharge from the hospital plus length of stay during a possible readmission

within 30 days from surgery. All randomised participants will be included in the analysis (intention-to-treat) if all data have been collected for 30 days postoperatively). The length of stay will be presented as a continuous numerical variable in the Result section of the manuscript. We expect that the data are not normally distributed due to the low number of participants, thus, medians and range for the intervention and control group will be presented. Furthermore, a Mann-Whitney U-test will be performed to compare the length of stay between the two groups.

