## Aim

The aim of the trial was to investigate if intraoperative intraperitoneal administration of fosfomycin, metronidazole and recombinant human granulocyte-macrophage colony stimulating factor followed by oral antibiotic for three days (intervention group) was as effective as the current intravenous antibiotic treatment given during and three days (control group) after appendectomy for perforated appendicitis. We evaluated this through length of stay.

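### The aim is to show equal effectiveness through length of stay, but the only primary inference is a test of no difference, so similar stays could not support the aim and the 48 h acceptable difference plays no part in the conclusion

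*SAP*

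**What the plan says.** - **Aim.** The question is whether the intervention "was as effective as the current intravenous antibiotic treatment given during and three days" after surgery. The Aim section adds: "We evaluated this through length of stay".
- **Sample size.** Cumulative 30-day stay "was expected to be 72 hours with a standard deviation of 12 hours in the control group", and "an acceptable difference between the groups was set at 48 hours". Alpha "was set at 0.05". Beta "was set at 0.80", which must mean power. The result is 4 per group, raised to 6.
- **Endpoints, Primary endpoint.** Medians and ranges are reported per group, and "a Mann-Whitney U-test will be performed to compare the length of stay between the two groups".
- **Statistical methods.** Data that look normal on histograms and Q-Q plots go to a t-test instead. A p-value of 0.05 or less counts as significant.

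The 48 h does not appear again after the Sample size section. The SAP plans no estimate of the between-group difference, no confidence interval, no test against a margin, and no rule for deciding that the aim has been met.

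**The concern.** An aim of equal effectiveness together with an acceptable difference reads as a non-inferiority or equivalence question. The Mann-Whitney test, and equally the t-test alternative, asks only whether there is evidence against no difference. The two can disagree in both directions:

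- A non-significant result may be read as equal effectiveness when the data do not exclude an excess of 48 h or more.
- A significant excess may be read as failure when the data show that it is smaller than the difference the SAP itself accepts.

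The Secondary endpoints section rules out testing of secondary outcomes, so this is the only planned outcome comparison. It determines what the trial may conclude.

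**Working it through.** **Inputs from the SAP.** Control stay 72 h, SD 12 h, difference 48 h, alpha 0.05 (two-sided assumed, as sidedness is not stated), power 0.80, 6 per group.

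**1. The SAP's own figure.**

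- *t-test:* noncentrality = 48 / (12 × √(2/n)). This is 4.0 at n = 2, 4.9 at n = 3 and 5.7 at n = 4, giving power of 56%, 95% and over 99%. So 3 per group would do.
- *Exact Mann-Whitney:* the smallest two-sided p is 2 / C(2n, n). That is 2/20 = 0.10 at n = 3, so significance is impossible, and 2/70 = 0.029 at n = 4, where simulated power is 97%. This gives exactly 4 per group.

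A non-inferiority calculation with true difference 0 and margin 48 h leads to the same numbers. The sample size therefore reproduces, but it does not show which hypothesis was meant.

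**2. The test and its matching interval at 6 v 6.** There are C(12, 6) = 924 rank arrangements. U = 5 gives p = 38/924 = 0.041 and U = 6 gives p = 0.065, so the critical value is 5. The matching interval runs from the 6th smallest to the 6th largest of the 6 × 6 = 36 pairwise differences. Its coverage is 1 − 38/924 = 95.9%.

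**3. Simulation (6 per group, normal data, equal SDs).** Excess means intervention minus control. SDs above 12 h are assumptions, shown for range because stay includes readmission hours.

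| SD (h) | True excess (h) | p ≤ 0.05 | Upper limit < 48 h |
|---|---|---|---|
| 12 | 0 | 4% | > 99% |
| 12 | 12 | 30% | 99% |
| 12 | 24 | 83% | 83% |
| 12 | 48 | about 99.99% | 2% |
| 24 | 0 | 4% | 83% |
| 24 | 48 | 83% | 2% |
| 30 | 0 | 4% | 64% |
| 30 | 48 | 64% | 2% |
| 36 | 48 | 49% | 2% |

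- *Significant but inside 48 h, SD 12 h:* the stay is significantly longer with the whole interval below 48 h in 29% of trials at a true excess of 12 h, and in 66% at 24 h.
- *Non-significant with a true 48 h excess:* about 0.01% at SD 12 h, then 17%, 36% and 51% at SD 24, 30 and 36 h.

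**4. Constructed data sets.** Control stays are 60, 66, 70, 74, 78 and 84 h.

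| Intervention | p | 95% interval (h) | Against 48 h |
|---|---|---|---|
| Each 24.5 h longer | 0.002 | 12.5 to 36.5 | Excluded, although significantly longer |
| 64.5, 68, 72, 76, 140, 200 h | 0.59 | −9.5 to 116 | Not excluded, although non-significant |
| Each 25.3 h shorter | 0.002 | −37.3 to −13.3 | Excluded; the planned test supports no worse |

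**The case against.** **The SAP never calls 48 h a margin and gives it no direction.** One could read 48 h as a shortening to be detected, from three days of intravenous treatment to an earlier discharge on oral treatment. On that reading, using it only for sample size alongside a difference test is ordinary practice. The sample size does not settle the matter. This stands in part: the first defect is an undefined hypothesis, and the remedy must be conditional on what was meant. But a difference described as acceptable is most naturally one to be tolerated, and under either reading the test cannot support equal effectiveness when stays are similar.

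**A reader might infer that no possible result could support the aim.** The documents do not support that. A significantly shorter intervention stay would support a no-worse reading, as the third constructed data set shows.

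**A reader might infer that misread non-significance is a large risk under the SAP's own assumptions.** It is not. At SD 12 h a true 48 h excess is missed in about 0.01% of trials. That risk arises only with larger SDs, which the SAP does not state.

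**A reader might infer that the margin would pass a treatment that fails through readmissions.** That needs invented stay and readmission times, and the Complications table would show readmissions by group.

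**The margin rule performs well on normal data, which the SAP does not expect.** This stands. With SD 12 h, no true difference, and an assumed 10% or 20% of patients in both groups readmitted for a further 72 to 96 h, the chance that the upper limit is below 48 h falls from over 99% to about 71% or 56%.

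**Group is the same as hospital (Design section).** This also stands. A hospital effect shifts the interval as much as it shifts the test.

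**Conclusion.** The concern holds in this form: the planned analysis cannot support the aim when stays are similar, and the 48 h plays no part in the conclusion. The mismatch is in the SAP's own wording and does not depend on the simulations, which show its size. At the planned SD the main conflict is a verdict of significantly longer for an excess that the SAP accepts (about 66% of trials at a true excess of 24 h). At larger, assumed SDs the opposite error appears as well. These rates assume normal data with equal SDs, a two-sided exact test and 6 per group. The stated sample size is not faulted here.

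**What to change.** In the Primary endpoint section:

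1. State whether the hypothesis is non-inferiority or equivalence, and give the direction and role of the 48 h.
2. Make the primary result the Hodges-Lehmann difference (intervention minus control, in hours) with its exact 95% interval. Use it whatever the histogram shows, so that the t-test switch does not apply to the primary outcome.
3. If 48 h is the margin, conclude non-inferiority only if the upper limit is below 48 h, or equivalence only if the whole interval lies within ±48 h. Otherwise report the result as inconclusive against the margin.
4. Keep the Mann-Whitney p-value as supplementary, and state that p > 0.05 is not evidence of equal effect.
5. Word the conclusion as one about hospital stay, and say that the interval does not remove the hospital effect.

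The cost is SAP wording and one added analysis of data already collected. The downside is that 12 patients may give an inconclusive answer if the SD is well above 12 h or readmissions skew the stays, more so for equivalence: with no true difference at SD 24 h, the equivalence rule succeeds in 66% of trials against 83% for non-inferiority.
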